## 8. PARTICIPANT IDENTIFICATION

### 8.1. Study Participants

Participants with compensated cirrhosis due to non-alcoholic fatty liver disease (CC-NAFLD), body mass index (BMI)  $\geq 30 \text{ kg/m}^2$  and aged  $\geq 18$  years.

### 8.2. Inclusion Criteria

- Participant is able to communicate in English and is willing and able to give informed consent for participation in the trial.
- Aged  $\geq 18$  years.
- BMI  $\geq 30 \text{ kg/m}^2$  (or BMI  $\geq 27.5 \text{ kg/m}^2$  for people of Black, Asian, or minority ethnic origin as per the NICE guidance for obesity screening)
- Diagnosed with CC-NAFLD based on one of the following
  - Biopsy with histological evidence of fibrosis score of 4 [with or without NASH (NASH defined as score of  $\geq 1$  for each of steatosis, inflammation, and ballooning) based on the NASH Clinical Research Network criteria
  - Previous biopsy with evidence of NASH but with current non-histological diagnosis of cirrhosis\*
  - Previous biopsy or imaging with evidence of hepatic steatosis but with current non-histological diagnosis of cirrhosis\*

[\**Definition of non-histological diagnosis of cirrhosis:*

Liver stiffness by transient elastography  $\geq 15 \text{ kPa}$  AND ANY of:

- imaging evidence of nodular OR irregular liver AND/OR
- presence of porto-systemic collateral vessels AND/OR
- splenomegaly (without alternative cause) AND/OR
- thrombocytopaenia in absence of primary haematological disease.]
- Stable dose of medication(s) for type 2 diabetes for at least 3 months prior to screening visit.
- Willing to allow his or her General Practitioner and consultant to be notified of participation in the trial.

### 8.3. Exclusion Criteria

The participant may not enter the trial if ANY of the following apply:

- Evidence for any of the following alternative or co-existing aetiologies: alcohol [alcohol screening tool (AUDIT-C) score  $\geq 8$ , and for patients for whom alcohol may have been a contributing factor to their diagnosis of cirrhosis, they will be excluded if they have any history of sustained harmful alcohol intake defined as  $\geq 35$  units for females and  $\geq 50$  units for males per week], active viral hepatitis (subjects cured for hepatitis C virus infection less than 2 years prior to screening are not eligible), haemochromatosis, primary biliary cholangitis, primary sclerosing cholangitis, Wilson disease, severe alpha-1-antitrypsin deficiency (ZZ phenotype), and autoimmune hepatitis
- Alcohol intake of  $\geq 18$  units for females and  $\geq 26$  units for males over the last 7 days, as per the NAFLD diagnostic criteria.
- Platelet count  $< 100 \times 10^9 \text{ cells/L}$  AND either medium (grade II) oesophageal or gastric varices with endoscopic high-risk stigmata (e.g., red signs), or large (grade III) varices on endoscopy within 1 year of screening [OR, IF NO ENDOSCOPY WITHIN 1 YEAR: exceeding the expanded Baveno VI criteria (platelet  $< 110 \times 10^9 \text{ cells/L}$  AND/OR stiffness  $> 25 \text{ kPa}$ )]
- History or presence of hepatic decompensation (jaundice, ascites, hepatic encephalopathy, or variceal haemorrhage)

- Model for end-stage liver disease (MELD) score  $\geq 13$
- Child-Pugh score  $\geq 8$
- Total bilirubin  $> 25.5 \mu\text{mol/L}$  (Note: Patients with documented Gilbert's syndrome but conjugated bilirubin within normal range are eligible).
- ALT  $\geq 5\times$  upper limit of normal.
- AST  $\geq 5\times$  upper limit of normal.
- INR  $> 1.3$
- HbA1c  $> 11.3\%$  ( $>100\text{mmol/mol}$ ).
- Insulin use for more than 10 years for type 2 diabetes management AND C-peptide  $<600\text{pmol/L}$ .
- Type 1 diabetes.
- Evidence of proliferative retinopathy.
- Listed for liver transplantation.
- History of hepatocellular carcinoma or history of hepatocellular carcinoma treatment.
- HIV infection
- Weight loss of 10% or more since diagnostic biopsy or, if biopsy not present, within the last 6 months.
- Previous bariatric surgery or ileal resection.
- History of biliary diversion.
- Acute cholecystitis or acute biliary obstruction.
- Contraindication to MRI.
- Documented arrhythmia, except atrial fibrillation, or prolonged QT syndrome.
- Taking warfarin.
- Chronic renal failure of stage 4 or 5.
- Scheduled for elective surgery under general anaesthesia
- Female participant who is pregnant, lactating, or planning pregnancy during the course of the trial.
- Any other significant disease or disorder which, in the opinion of the Investigator, may either put the participants at risk because of participation in the trial, or may influence the result of the trial, or the participant's ability to participate in the trial.
- Currently taking part in other interventional clinical trials unless approved by the CI.

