#### **Pre-specified clinical events judged as SAEs**

As one of the aims of the trial is to assess whether the intervention prevents progression of compensated cirrhosis to decompensation, the following events will be judged as SAEs:

- At least one event of hepatic decompensation:
  - Jaundice
  - Ascites
  - Hepatic encephalopathy
  - Variceal haemorrhage
- Liver transplantation or qualification for liver transplantation, defined as a MELD score  $\geq 15$
- Hepatocellular carcinoma.

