| 4             | 3.0                  | 23-Feb-22   | [name] | 
 
1. Addition of hand-grip strength measurement to allow for calculation of an additional marker of physical performance: the liver frailty index.
 
                                                                                                                                                      |

|   |     |           |                       |                                                                                                                                                                                                                                                                                                    |
|---|-----|-----------|-----------------------|----------------------------------------------------------------------------------------------------------------------------------------------------------------------------------------------------------------------------------------------------------------------------------------------------|
| 5 | 4.0 | 11-Jul-22 | [name] | 1. Change of exclusion criteria to allow patients with type 2 diabetes on insulin.                                                                                                                                                                                                                 |
| 6 | 5.0 | 17-Aug-22 | [name] | 2. Rewording of exclusion criterion for clarity from “no evidence of proliferative retinopathy” to “evidence of proliferative retinopathy”                                                                                                                                                         |
| 7 | 6.0 | 16-Dec-22 | [name] | 1. Addition of a participant identification centre                                                                                                                                                                                                                                                 |
| 8 | 7.0 | 19-Dec-22 | [name] | 1. Addition of 2 more research sites.
2. Clarification that MRE will happen only in sites with relevant infrastructure.
3. Changes to the exclusion criteria to allow the broadening of inclusion criteria for patients with low-risk varices and those without harmful alcohol consumption. |

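### Section 8.3 varices exclusion: at platelets of 100 × 10⁹/L or more, high-risk varices seen at endoscopy do not trigger it, although some of the same patients would be excluded had no endoscopy been done

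*Protocol*

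**What the plan says.** Section 8.3 of the protocol opens with "The participant may not enter the trial if ANY of the following apply", so each bullet is sufficient on its own. The varices bullet has two limbs:

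- **Endoscopy within 1 year.** A platelet count below 100 × 10⁹/L "AND either medium (grade II) oesophageal or gastric varices with endoscopic high-risk stigmata (e.g., red signs), or large (grade III) varices on endoscopy".
- **No such endoscopy.** The bracketed alternative begins "IF NO ENDOSCOPY WITHIN 1 YEAR: exceeding the expanded Baveno VI criteria" and gives the limits as platelets below 110 × 10⁹/L "AND/OR stiffness" above 25 kPa.

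Two other bullets bear on the same patient. One excludes "History or presence of hepatic decompensation (jaundice, ascites, hepatic encephalopathy, or variceal haemorrhage"). The other is the general clause, which begins "Any other significant disease or disorder which, in the opinion of the Investigator, may either put the participants at risk because of participation in the" and so rests on judgement.

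Elsewhere, section 10.1 lists "Variceal haemorrhage" among the clinical events judged in advance to be SAEs, and section 6 makes safety signals a co-primary objective. The amendment history in Appendix F says that exclusion criteria were changed to "allow the broadening of inclusion criteria for patients with low-risk varices".

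**The concern.** The no-endoscopy limb uses platelets and stiffness as a stand-in when nobody has looked for varices. The endoscopy limb applies when someone has looked. One would expect a finding of high-risk varices to be treated at least as strictly as the suspicion of them. As worded, over part of the range it is treated less strictly.

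Endoscopy is not in the schedule of procedures (Appendix B), so which limb applies depends on whether routine care happened to include one. Two patients with the same platelets and stiffness can then get opposite answers, and the one with the proven lesion is the one not excluded.

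The trial has 24 participants and safety is co-primary. A variceal bleed is an SAE by definition, and the section 11.6 stopping cut-off applies only while the control group has had no SAE. The rule for admitting patients with known varices should therefore be deliberate and read the same way at all three recruiting sites.

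**Working it through.** No sample size, power or alpha figure bears on this point. The check is a logical one on the wording of section 8.3.

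**Notation.** P is the platelet count (× 10⁹/L) and S is liver stiffness (kPa). V is true if endoscopy shows grade II varices with high-risk stigmata, or grade III varices.

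**Rules as written.**
- Endoscopy within 1 year: excluded if P < 100 and V.
- No endoscopy within 1 year: excluded if P < 110 or S > 25.

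**Illustrative values put in, for a patient in whom V is true:**

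| P | S | Endoscopy done, V seen | No endoscopy |
|---|---|---|---|
| 90 | 20 | excluded | excluded |
| 90 | 30 | excluded | excluded |
| 105 | 20 | not excluded | excluded |
| 105 | 30 | not excluded | excluded |
| 120 | 20 | not excluded | not excluded |
| 120 | 30 | not excluded | excluded |

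**Where the limbs conflict.** The reversal needs the second rule to exclude and the first not to: (P < 110 or S > 25) and P ≥ 100. This reduces to P of 100 to 109 at any stiffness, or P ≥ 100 with S > 25. At P ≥ 110 with S ≤ 25 neither limb excludes. At P < 100 with V seen, both do.

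**Can the region be reached?** Yes. The non-histological definition of cirrhosis in section 8.2 needs stiffness of at least 15 kPa and sets no upper limit. No other criterion sets a platelet limit.

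**Other readings of the sentence.**
- *The bracket sits under the platelet condition.* Without an endoscopy, exclusion would then need P < 100 and (P < 110 or S > 25). Since P < 100 implies P < 110, this is simply P < 100. The conflict disappears, but the 110 cut-off and the stiffness test do no work. Proven high-risk varices at P ≥ 100 are still not excluded.
- *The platelet condition attaches to grade II only, and grade III stands alone.* The word *either* comes after the AND and before both findings, which ties both to platelets. Even on this reading, grade II with stigmata at P ≥ 100 is not excluded and the conflict remains for it.

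**Do other criteria fill the gap?** The decompensation bullet covers a bleed, not varices that have not bled. The MELD, Child-Pugh, bilirubin and INR limits do not mention varices. That leaves the investigator-judgement bullet.

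**The case against.** The strongest reply has five parts.

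1. **The reversal is not general.** A reader might infer that a patient with proven high-risk varices and platelets of 100 or more would always be excluded without an endoscopy. That is not so: at 120 and 20 kPa neither limb excludes. This stands, and the point is limited to the region derived above.

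2. **Not excluded by this bullet is not the same as eligible.** A reader might infer that a site could not keep such a patient out. The investigator-judgement exclusion allows it to, the other criteria still apply, and section 9.4 requires a final eligibility check before randomisation. This stands and lowers the consequence. But judgement is discretionary and can differ between sites, so it does not replace a clear rule.

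3. **The amendment log proves nothing.** A reader might take its mention of low-risk varices as proof that the AND is a slip. A one-line log entry is only context for intent, and section 8.3 states no such purpose. The conjunction may be deliberate. This stands; the inconsistency rests on section 8.3 alone.

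4. **The harm is not quantified.** One bleed would be 1/16 = 6.25% of the intervention arm or 1/8 = 12.5% of the control arm, but that is true of any single event and does not measure the effect of this wording. There is also a randomised control group, and the TSDMEC reviews SAEs as they occur (section 13.3.2). This stands.

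5. **Removing the platelet condition would be a clinical choice.** A reader might infer that it should go. The documents do not settle that, and this review takes no position.

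None of the five makes the two limbs agree.

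**Conclusion.** The bullet is wrong as written. At platelets of 100 × 10⁹/L or more, its endoscopy limb excludes nobody. At platelets of 100 to 109, or at 100 or more with stiffness above 25 kPa, a patient whose varices are only suspected is excluded, while one whose high-risk varices have been seen is not excluded by this criterion. The only safeguard naming no threshold is investigator judgement.

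This rests on the literal reading, in which AND governs both varices findings and the bracket is a stand-alone alternative. The reading that removes the conflict leaves two stated thresholds without effect, so the sentence needs rewriting either way.

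The size is the extent of that region, not a number of patients. The documents give no frequency of high-risk varices at these platelet counts and no bleeding rate, so no expected number of affected participants or events can be derived. The wording does not show that the sponsor intended to admit high-risk varices, nor that any such patient has been enrolled.

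**What to change.** Issue a short eligibility amendment to section 8.3 in which the clinical leads:

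- reconcile the two limbs;
- state explicitly whether the platelet condition is meant to apply to high-risk varices proven at endoscopy;
- write the limbs as two separate, unambiguous exclusions, one for patients with an endoscopy within 1 year and one for those without, so that a positive endoscopy is not treated more leniently than no endoscopy by accident of wording.

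If the difference between the limbs is intended, the protocol should say so and give the reason. Which clinical rule applies is for the clinical leads to decide.

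The cost is one amendment and no new procedure. Depending on how the limbs are reconciled, some patients now admissible may no longer be.

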## 9. PROTOCOL PROCEDURES

A schedule of procedures is available in Appendix B.

### 9.1. Recruitment

Participants will be recruited from OUH, LUH, and PHU. The Royal Berkshire Hospital NHS Foundation Trust will act as additional participant identification centre.

During the course of the patients' regular clinical appointment, clinicians will give those patients that are potentially eligible a participant information sheet. Following verbal consent, participants will be introduced to the research team for an eligibility assessment and a detailed discussion of the study at the end of their clinical appointment. The clinical team will also send invitation letters to potentially eligible participants. For participants who chose to contact the research team later or over the phone, the research team will explain the study and assess their eligibility over the phone.

In participant identification centres, clinicians will screen their clinic lists to identify potentially eligible participants. They will approach potentially eligible participants during the course of their routine appointment or send them letters inviting them to take part. They will check their medical history to see if they are likely to meet the inclusion and exclusion criteria and provide them with the participant information sheet. Participants who are interested to take part will be referred to one of the research sites (e.g., participants from Royal Berkshire NHS Foundation Trust will be referred to OUH) where the screening procedures and provision of informed consent will take place.

As part of the screening process, but after providing written informed consent, weight and height will be measured and a blood test will be performed at the hospital. Females may be asked to have a pregnancy test to confirm that they are not pregnant. They may also be advised to use an effective method of contraception for the duration of the trial, and we will provide them with information on suitable contraceptive methods, as necessary. Consented participants who are keen to proceed and who are potentially eligible will be booked for a baseline visit.

### **9.2. Informed Consent**

The participant must personally sign and date the latest approved version of the Informed Consent form before any trial specific procedures are performed.

Written and verbal versions of the Participant Information and Informed Consent will be presented to the participants detailing no less than: the exact nature of the trial; what it will involve for the participant; the implications and constraints of the protocol; the known side effects and any risks involved in taking part. It will be clearly stated that the participant is free to withdraw from the trial at any time for any reason without prejudice to future care, without affecting their legal rights and with no obligation to give the reason for withdrawal.

The participant will be allowed as much time as wished to consider the information, and the opportunity to question the Investigator, their GP or other independent parties to decide whether they will participate in the trial. Written Informed Consent will then be obtained by means of participant dated signature and dated signature of the person who presented and obtained the Informed Consent. The person who obtained the consent must be suitably qualified and experienced, and have been authorised to do so by the Chief/Principal Investigator. A copy of the signed Informed Consent will be given to the participant and a copy will be filed in the medical notes. The original signed form will be retained at the trial site.

### **9.3. Screening and Eligibility Assessment**

The screening procedures will initially involve checking the medical history and a brief interview to check concomitant medication, contraindications to MRI, and further eligibility criteria as listed in section 8. As per Appendix B, participants will be required to take a blood test and a measurement of weight and height. Their medical history and concomitant medication will be reviewed. They will also complete the 3-item Alcohol Use Disorders Identification Test consumption questionnaire (AUDIT-C).

Following completion of the screening visit, the maximum duration between the screening visit and randomisation will be 4 weeks (28 days). After this period has passed and participants are still keen to participate, the screening blood test must be repeated to allow for an up-to-date measurement (e.g., during their baseline visit). In all cases, the screening blood test will need to occur within 28 days before randomisation.

Participants should also have their baseline assessment (section 9.6) during the window between screening visit and randomisation. If the baseline visit brings forth reasons to exclude the patient (e.g., participant is unable to undertake the MRI scan due to claustrophobia), the participant must not be

randomised; they will be regarded as screen failure, and will be replaced. Protocol waivers are not permitted.

Participants will not be randomised if a baseline visit has not been completed within 16 weeks from provision of informed consent. This cut-off will be in place to facilitate recruitment.

#### **9.4. Randomisation**

Consented participants will be individually randomised with a 2:1 allocation to receive either the intervention or care as usual through minimisation with a 20% random element. The two stratified variables are BMI ( $\geq$ / $<$  35 kg/m^2) and type 2 diabetes (yes/no), as these are prognostic factors of clinical outcomes.

Randomisation will occur after the baseline visit has been completed and a final check ensuring that all eligibility criteria have been met. To allow time for the analysis of the blood sample, the window between the end of the baseline visit and the randomisation will be within 24 hours.

The CI will programme the randomisation software (MinimPY). The software is validated and there will be no paper-based back-up randomisation procedure in case of emergencies. Upon completion of the baseline visit, the researcher carrying out the baseline visit will submit a request for randomisation via phone call to an independent researcher including the values of the stratification variables for the participant who completed the baseline visit. The independent researcher will run the minimisation software that will allocate the participant to one of the two groups and inform the CI of the group allocation over the phone. The CI will inform the participant of the group allocation over the phone, so that the participant does not need to return for a randomisation visit.

Allocation concealment is achieved by

- concealing the processes of recruitment, screening, and eligibility assessment from the researcher performing the randomisation centrally
- performing the randomisation following the baseline visit
- not carrying out baseline visits for additional participants during the run-in period between the baseline visit of a participant and their randomisation.

#### **9.5. Blinding and code-breaking**

It is impossible to blind the participants and clinicians to the treatment due to the nature of the intervention. Therefore, procedures for breaking the allocation code are not applicable. The independent assessor of the MRI/MRE scans (for the assessment of the primary outcome) will be blinded to allocation.

#### **9.6. Description of study intervention, comparator, and study procedures (clinical)**

##### **9.6.1. Description of study intervention**

The intervention is a low-energy total diet replacement programme with behavioural support (TDR) and has three phases.

In phase 1 (sole source TDR, weeks 0-16), participants will consume a nutritionally complete package of 4 formula products per day [soups, shakes, and bars (860 kcal/day)].

In phase 2 (food-re-introduction, weeks 17-22), products will be gradually reduced and replaced with food-based meals. During this phase, participants will consume 3 products per day for weeks 17-18, 2

products per day for weeks 19-20, and 1 product per day for weeks 21-22 together with food-based meals.

In phase 3 (weight maintenance, weeks 23-24), participants will consume food-based meals.

Participants will have contact with the dietitian for around 15 minutes each week (or 30 minutes fortnightly) over the 24 weeks for behavioural support (for details on the structure and content of sessions please see Appendix C). This will be over the phone or the app depending on participant preference.

The intervention including formula products and consultations will be donated by Nestle Health Science and Oviva, respectively (see section 17.1). Participants may choose to receive the formula products during their study assessments, by post, or a combination of both. Management of the stock of products (e.g. delivery, labelling, distribution, storage, and replacements) will follow a study-specific SOP.

Participants in the intervention group will continue to receive care as usual.

